**Methods:**

The study will be a randomised controlled study with parents and their new-born child/ren who are seen at 6–12 weeks of age by a child/community health nurse. Consenting parents will complete a questionnaire on oral health knowledge, behaviours, self-efficacy, oral health fatalism, parenting stress, prenatal and peri-natal health and socio-demographic factors at study commencement and at 12 and 36 months. Each child–parent pair will be allocated to an intervention or a standard care group, using a computer-generated random blocks. The standard group will be managed through the standard early oral health screening program; “lift the lip”. The intervention group will be provided with tailored oral health counselling by oral health consultants trained in MI and AG.

Participating children will be examined at 24, and 36 months for the occurrence of dental decay and have their height and weight recorded. Dietary information obtained from a food frequency chart will be used to determine food and dietary patterns. Data analysis will use intention to treat and per protocol analysis and will use tests of independent proportions and means. Multivariate statistical tests will also be used to take account of socio-economic and demographic factors in addition to parental knowledge, behaviour, self-efficacy, and parent/child stress.

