1. *Measure the baseline oral health knowledge, behaviour, attitudes, self-efficacy of parents/caregivers and parental stress levels of new-born children and then to measure and compare the change in these factors among the intervention and control groups at 12 and 36 months.* These factors are expected to be influential in affecting the oral health of children. The hypothesis tested is that early oral health promotion intervention will change the oral health knowledge, behaviour, attitudes, self-efficacy and parental stress levels to achieve improved oral health*.*

2. *Measure and compare the occurrence of early childhood dental decay among the intervention and control groups.* The hypothesis tested is that early health promotion will reduce the incidence of dental decay.

3. *Measure and compare the consumption of cariogenic/obesogenic foods and drinks and the growth and development of the child study participants.* The hypothesis tested is that early childhood oral health promotion will reduce consumption of cariogenic/obesogenic foods and the prevalence of early childhood adiposity.

4. *Compare the decay experience and increment and childhood adiposity among children in the intervention and control groups when the children are older, at pre-primary school age (2 years post active intervention, approximately 5 years of age).* The hypothesis being tested is that early intervention with AG and MI will have longer lasting effects beyond the immediate intervention in early childhood and the benefits are retained into the period when the permanent teeth are becoming established.

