The self-completed questionnaire will collect socio-demographic (age, sex, education level, family income, Aboriginality) and psychosocial information (oral health-related self-efficacy, knowledge about appropriate baby bottle use and children’s oral hygiene and belief in oral fatalism, instrumental social support and parental stress) and parental perceptions of treatment need and oral health care behaviours. The psychosocial measures have been used in other studies and have had their psychometric properties validated [38,39].

The psychosocial measures are shown in List of Psychocosial Measures. Oral health self-efficacy comprised nine items scored on a Likert scale from 1 (not at all confident) to 4 (very confident); higher scores indicate greater self-efficacy. Oral health knowledge on appropriate use of baby bottle and children’s oral hygiene comprise 10 items scored on a Likert scale from 1 (strongly agree) to 5 (strongly disagree); higher scores indicate better knowledge. Oral health fatalism comprised one item, “Most children eventually develop dental cavities”, scored 1 (strongly agree) to 5 (strongly disagree). The parenting stress instrument comprised six items scored on a Likert scale, 1 (never) to 5 (almost always); higher scores indicate higher levels of stress. The social support instrument comprised four items scored “yes” or “no”. Mean scores from sum of the item scores will be used for the oral health self-efficacy, oral health knowledge and parenting stress scales while the oral health fatalism score will be converted to a binary variable reflecting parent/caregiver agreement with the statement and each item of the instrumental social support instrument will be  presented as frequency scores and used as a binary variable.List of Psychological measures 

Oral Health Self-efficacy; scale, 1 = not at all confident, 4 = very confident

How confident do you feel that you are able to make sure that your child’s teeth are brushed before bedtime when you are:

1. Under a lot of stress?

2. Depressed?

3. Anxious?

4. Feeling like you do not have time?

5. Tired?

6. Worrying about other things in your life?

7. Bothered by your child crying?

8. Bothered because your child doesn’t stay still when you want him or her to brush?

9. Told by your child that he/she does not feel like brushing right now?

Knowledge of bottle use; scale, 1 = strongly agree, 5 = strongly disagree

1. Putting a baby to bed with a bottle helps the child to be better fed.

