2. Putting a baby to bed with a bottle helps the child sleep better.

3. Putting a baby to bed with a bottle helps the child to gain weight and grow.

4. There is nothing wrong with putting the baby to bed with a bottle.

Knowledge of children’s oral hygiene; scale, 1 = strongly agree, 5 = strongly disagree

1. Cavities in baby teeth don’t matter since they fall out anyway.

2. Keeping baby teeth clean is not very important; after all, they fall out.

3. There is not much I can do to stop my child from developing dental cavities.

4. There is not much I can do to help my child have healthy teeth.

5. Children don’t need to brush everyday until they get their permanent teeth.

6. Children don’t really need their own toothbrush until all their teeth come in.

Oral health fatalism; scale 1 = strongly disagree, 5 = strongly agree

1. Most children eventually develop dental cavities.

Parental stress; scale 1 = never, 5 = almost always

1. How often do you feel that you have too little time to spend by yourself?

2. How often do you wish you did not have so many responsibilities?

3. How often would you say your child (or children) gets on your nerves?

4. How often do you feel that your child/ren is/are making too many demands on you?

5. How often do you feel that being a parent is much more work than pleasure?

6. How often do you feel tired, worn out, or exhausted from raising a family?

Instrumental support; scale “yes”, “no”

If you need to, is there someone you can count on to……

1. ……Run errands for you?

2. ……Lend you money?

3. ……Watch over your child/ren?

4. ……Lend you their car or give you a lift?

We will also seek information relating to the mother’s health during the last trimester of pregnancy and the child’s health in the peri-natal period at base-line. The weight and height of each child and primary caregiver will be measured at 24- and 36- month follow-up visits. Parents will recall 24-hour and usual dietary information for each child using a self-administered short food and beverage frequency questionnaire at the 12- and 36-month follow-ups. The 12- and 36-month questionnaire will also collect information relating to oral health care behaviours for the child including toothbrushing and use of fluoride toothpastes, fluid consumption, and use of professional oral health care services.

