### Procedures

The OHC will undertake the first counselling session (home visit, expected to last up to 30 minutes) within 4 weeks after consent with two additional counselling sessions, negotiated between the OHC and the study participant as to face-to-face or phone contact, in the first 6 months (expected to last 15–30 minutes). The protocol for MI/AG will be adapted from Weinstein et al. and Plutzer & Spencer [30,34].

The MI/AG approach will follow a structured approach of rapport establishment and identification of oral health and nutritional needs using empathic reflective listening; presentation of menu of options and information with permission; discussion of options and elicitation of “change talk”; elicitation of importance and confidence in behavioural change; the development of behaviour change plan; and a schedule of follow-up. All discussions will be undertaken in a collaborative, person centred approach central to the MI “spirit”. Whilst the menu will present a range of options with potential to affect early childhood dental decay, the discussion will be limited to one or two topics of primary concern to the study participant, in keeping with the MI approach. Negative responses during the counselling session will be accepted without rebuttal and issues left for exploration at a subsequent session. AG will follow the anticipated milestones of teething and transition from wholly breast- or formula-fed to solid foods. Again, topics for discussion will arise in conversation with the study participant with guidance from the counsellor and the counsellor will provide information only when requested to do so. The information will incorporate appropriate dietary and nutritional guidance, following the national guidelines, to assist in the development of healthful behaviours, with the counsellors linking oral and general health impacts of these behaviours [48]. Review of audio recordings of counselling sessions will be undertaken to monitor protocol compliance.

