### Measures

The primary outcome measures are the incidence of dental decay in primary teeth and the prevalence of obesity. Children will be examined at the dental therapy clinics of the DHS of Western Australia for the incidence of dental decay by two blinded, calibrated examiners at 24 and 36 months of age, using the criteria specified by Workshop on Reporting Early Childhood Caries [51] and at 60 months using the criteria of the WHO [52].

Examiner training will involve examination of early childhood decay under the guidance of a specialist paediatric dentist. Further examiner calibration will be undertaken by examination of 10 children consenting to participate in an oral screening program of DHS. During field examinations, approximately 5% of study participants will be re-examined to test for intra- and inter-examiner reliability. Child height/length and weight will be measured and Body Mass Index calculated (BMI; weight/height^2^) and BMI z score determined at 24 and 36 months, using the age-specific WHO growth standards [53]. Number needed to treat as an effect measure of the program will be estimated [54]. Examiner training will be repeated for each cycle of the clinical examinations to maintain reliability over the course of the study.

Secondary outcome measures will be changes in knowledge, attitude, behaviour and self-efficacy of parents towards the oral health of their child and differences in nutritional and dietary patterns between groups. Long-term outcomes will be the incidence of dental decay and referral for care under general anaesthesia among the groups when the child is 5 years of age.

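### Self-efficacy and child oral-care behaviour are defined as change from a 6–12-week baseline that is hypothetical for the first and not identified for the second; compare the arms at follow-up instead

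*Protocol article*

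**What the plan says.** The Abstract (Methods) recruits families "who are seen at 6–12 weeks of age by a child/community health nurse". Parents complete the questionnaire, which includes behaviours and self-efficacy, "at study commencement and at 12 and 36 months".

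Aim 1, at the end of the Background, is to take baseline values and then "measure and compare the change in these factors among the intervention and control groups at 12 and 36 months". The Measures section repeats this: "Secondary outcome measures will be changes in knowledge, attitude, behaviour and self-efficacy of parents towards the oral health of their child".

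In the Methods, the nine self-efficacy items share one stem, which asks how confident the parent is of being able to "make sure that your child’s teeth are brushed before bedtime when you are" in a given state. Item 8 supposes a child who will not keep still for brushing. Item 9 is "Told by your child that he/she does not feel like brushing right now". Each item is scored 1 to 4, and a mean score is derived from the item sum. The item list shows no separate wording for the infant period. Under Procedures, "AG will follow the anticipated milestones of teething", so the first teeth are treated as a future event when counselling starts.

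On behaviour, the Methods state: "The 12- and 36-month questionnaire will also collect information relating to oral health care behaviours for the child". The items named are toothbrushing, fluoride toothpaste, fluid consumption and use of professional services. The description of the self-completed questionnaire also lists oral health care behaviours, without saying whether the parent's or the child's.

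**The concern.** A change outcome needs a baseline that measures the same thing as the follow-up. Here there are two gaps.

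- **Self-efficacy.** At 6–12 weeks the parent has no teeth to brush and no child who can refuse in words. The answer is a forecast of confidence. At 36 months the same items can draw on experience. The difference mixes a real change in confidence with the items becoming applicable.
- **Child oral-care behaviour.** The follow-up items have no identified counterpart at baseline, so the promised change cannot be derived from them as the article stands.

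At stake are the interpretation and precision of two secondary outcomes. The article gives the instrument, its timing and the outcome definition, and an analysis plan cannot supply a baseline that was not collected.

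**Working it through.** **1. Reproducing the plan's figure.** The article gives no figure for these outcomes. I use its 514 per arm as an illustrative analysed number, so I checked it first. From Sample size and power: dmft 1.26 against 0.8 (difference 0.46), SD 2.63, two-sided 5%, power 80%.

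n = 2 × (1.960 + 0.842)² × 2.63² / 0.46² ≈ 513.1, rounded up to 514. It reproduces.

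**2. Does an applicability shift bias the randomised comparison?** Let both arms gain the same amount s between baseline and follow-up because the items become answerable from experience. With b and f the mean baseline and follow-up scores without that shift:

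- within-arm change = (f + s) − b, which contains s;
- between-arm difference in change = [(f₁ + s) − b₁] − [(f₀ + s) − b₀] = (f₁ − b₁) − (f₀ − b₀), which does not.

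A simulation (4,000 runs, 514 per arm, s = 0.4 SD, correlation 0.2, no true effect) agrees: mean within-arm change 0.40 SD, mean between-arm difference 0.00.

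**3. What does subtracting a weak baseline cost?** Assume equal SDs at baseline and follow-up, and a correlation ρ between them. The documents give no ρ, so a range is shown. The detectable difference in SD units is:

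- follow-up score alone: (1.960 + 0.842) × √(2/514) = 0.175
- change score: 0.175 × √(2(1 − ρ))
- follow-up score with baseline as covariate: 0.175 × √(1 − ρ²)

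| Assumed ρ | Follow-up alone | Change score | Baseline as covariate |
|---|---|---|---|
| 0 | 0.175 | 0.247 | 0.175 |
| 0.2 | 0.175 | 0.221 | 0.171 |
| 0.3 | 0.175 | 0.207 | 0.167 |
| 0.5 | 0.175 | 0.175 | 0.151 |
| 0.7 | 0.175 | 0.135 | 0.125 |

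Below ρ = 0.5 the change score is less precise than ignoring baseline altogether; its variance is 2.0 times as large at ρ = 0 and 1.6 times at ρ = 0.2. The covariate analysis is never worse than the change score, because 1 − ρ² = (1 − ρ)(1 + ρ) ≤ 2(1 − ρ).

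**4. How much of the scale is affected?** Items 8 and 9 are 2/9 (22%) of the mean score. The brushing stem covers all nine, so dropping those two items would not remove the difficulty.

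**5. Behaviour, side by side.** Aim 1 and Measures promise a change in behaviour. The Methods place the named child oral-care items at 12 and 36 months. In the same paragraph, maternal and perinatal health are expressly assigned to baseline. The only baseline candidate is the unspecified behaviour content of the self-completed questionnaire.

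**The case against.** The strongest defence is that the stem asks about perceived ability, which a parent can answer in advance. The protocol also says the measures were validated in other studies, and Aim 1 compares change between randomised arms, where a common shift cancels. All of this stands. It rules out saying that self-efficacy cannot be validly measured at baseline, although the article does not give the child ages in the validation work, so suitability at 6–12 weeks is not shown either.

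A reader might infer four stronger things that the documents do not support.

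- **The between-arm result is biased.** That would need applicability to shift differently by arm, for example if counselling alters when brushing begins. This is possible, but nothing in the documents sizes it.
- **Blank items 8 and 9 produce a spurious rise**, for example from 28 to 36 on a raw sum for a parent who is very confident throughout. This requires blanks to be counted as zero. No such rule is stated, and zero is not on the 1–4 scale. With a mean over answered items the same parent scores 4 each time. Handling of blank items may properly sit in the analysis plan.
- **Behaviour change cannot be computed for anyone.** The Abstract and Methods do list behaviours in the questionnaire, so the fault is an unidentified match, not a proven absence.
- **The mediation analysis is compromised.** Data analysis does not say that change scores enter it.

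Whether items 8 and 9 suit a 12-month-old rests on child development and not on anything in the documents. It is plausible for item 9 and weak for item 8, so I do not rely on it.

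**Conclusion.** The point holds in a limited form. Two secondary outcomes are framed as change from a baseline that is largely hypothetical (self-efficacy) or not identified (child oral-care behaviour). The consequences are a within-arm change that cannot be read as a change in confidence, and a possible loss of precision. If the baseline carries no information (ρ = 0), the detectable difference rises from 0.175 to 0.247 SD; at ρ = 0.2 it is 0.221 SD; at ρ = 0.5 there is no loss against the follow-up score alone, and above that the change score gains on it. Adjusting for baseline is at least as good throughout.

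These figures assume 514 analysed per arm, equal SDs at the two times and an assumed correlation. A low correlation is plausible for answers given before there are teeth to brush, but the documents do not establish it. The decay and obesity primary outcomes are not touched.

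**What to change.** - Restate the self-efficacy outcome as the between-arm difference in the same nine-item mean score at 12 and at 36 months, with the baseline score as a covariate and not subtracted. Keep all nine items at every time point: a shorter early version would retain the stem and create a scale mismatch.
- Do not interpret within-arm change in self-efficacy.
- Restate the child oral-care behaviour outcome as the between-arm difference at 12 and at 36 months, and say which behaviours in the baseline questionnaire, if any, have a follow-up counterpart.

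This changes outcome wording and the analysis model only; no new data are needed. The small cost is that within-arm change is no longer reported as an outcome.

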Dietary related information collected via a 24 hour recall questionnaire will be coded for cariogenic potential of the foods and drinks using the approach outlined by Lee and Messer (2010) [42] and the approach outlined by Bennet et al. (2009) for obesogenic potential of the foods and drinks [43].

The intervention group will be provided with oral health promotion delivered by a trained dental assistant (oral health counsellor, OHC) using the MI/AG protocol. The training of the counsellors involved a workshop comprising two days of didactic presentations, role-playing exercises and a practice counselling session with a parent–child dyad at the DHS’ School Dental Therapy training facility. An evaluation of the training program was undertaken and consisted of a MI pre- and post-test knowledge–base questionnaire, a Helpful Response Questionnaire and a trainer evaluation questionnaire. The knowledge and trainer evaluation questionnaires were based on those developed by Yale University School of Medicine [44]. The Helpful Response Questionnaire utilised was developed by Miller et al. [45].

At this stage, preliminary analyses have been undertaken of the OHCs’ knowledge of MI and trainer evaluation. The questionnaire to assess the OHCs' knowledge of the principles and practices of MI was administered as a pre–test (immediately before training) and post–test (immediately after training). It consisted of ten multiple-choice questions. OHCs scored one point for each correct answer.

From a maximum possible score of 10, the OHCs’ knowledge pre–test mean score was 4.3 (SD = 1.49) and post–test score was 6.4 (SD = 1.43). Comparison of mean scores using a paired two–sample t–test revealed a statistically significant difference *(p = 0.01).* It was concluded that the two-day training workshop increased OHCs’ knowledge of MI principles and practices. Full details of the evaluation of the training workshop for OHCs will be presented elsewhere (Manuscript in preparation).

Monitoring, feedback and improvement of the OHCs’ competence in the use of MI is on-going through the analysis of audio recordings.

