### Sample size and power

Sample size of approximately 514 children in each arm of the trial is required to detect a 35% reduction in dental decay experience [based on decay experience of children within DHS; dmft 1.26 (SD 2.63), test dmft 0.8] with a probability of 0.8 (power 80%) and rejecting the likelihood of no difference at probability 0.05 (α = 0.05) [49]. This is a conservative sample allowance to detect a difference, since an Australian intervention study on early childhood decay found 79% reduction in decay incidence among 20 month-old children [23]. Allowing for drop-off and loss to follow-up over the following 3 years, an initial sample of approximately 750 in each group of the trial would be required (an earlier study of caries prevention within SDS found attrition rate of 9% per annum over two years [50]). The estimated sample size will have a power of 94% to detect a 35% reduction in the prevalence of early childhood decay (dmft > 0; from 0.25 to 0.16) between the groups (α = 0.05). The estimated sample size will also permit detecting a 33% difference in prevalence of overweight or obese children between the two groups (from 20% to 14%) with 80% power and α = 0.05.

Ethical approval for the study has been provided by the University of Western Australia Human Research Ethics Committee (RA/4/1/4469), the Princess Margaret Hospital for Children Ethics Committee (Reg. No. 1900/EP), and the WA Country Health Services Ethics Committee (ref 2011:05). Figure 1 shows the study sample and pathway for the study participants in the test and control arms. All child participants will have the same clinical and other information collected again at approximately 5 years of age. Sample maintenance strategies, including card mail-outs on the child’s birthday, change of address notification and regular updating of the study will be undertaken.

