### Data analysis

Oral health outcomes will be defined by counts of decayed, missing and filled teeth/surfaces and include non-cavitated lesions. Predictor variables will be on the basis of group allocation to intervention or control group and the posited psychosocial mediating variables will be defined using the approach adopted by Finlayson et al. [39].

Appropriate parametric and non-parametric statistics will be used to test the aims of the study. Differences in outcomes between the groups will be tested on an intention to treat and per protocol basis. Univariate analyses using t-tests for continuous variables (*oral health knowledge, behaviour, attitudes, self-efficacy and parental stress of parents/caregivers*), and Chi square analyses for categorical variables will be undertaken to examine the baseline factors and their association with group assignment. Univariate analyses will also be used to examine the association between the primary outcomes of dental decay incidence and prevalence, and early childhood obesity prevalence, with group allocation.

Multivariate analysis will be used to control for potential confounding factors to examine the effects of treatment strategies, and will use linear regression for continuous outcome variables and test for mediator effects using the approach outlined by MacKinnon and Luecken (2011) [56], logistic regression for binary outcomes (dental decay prevalence, obesity prevalence) and Poisson regression to estimate rates of disease occurrence. Site-specific measures of caries incidence within an individual will use GEE analysis to control for correlation within an individual. Effect size will be estimated through calculation of incidence density ratios for dental decay and prevalence ratios for obesity. Effect measures will also be presented through calculation of number needed to treat and its associated 95% confidence interval. The statistically significant level will be at α = 0.05.

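### Only intervention children share counsellors, but the sample size and the named tests make no allowance for it; if outcomes differ between counsellors, the 80% power is too high

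*Protocol article*

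**What the plan says.** Under Methods, the Protocol article randomises individual child-parent dyads, stratified by location (Perth or Bunbury/Busselton). The intervention is counselling "delivered by a trained dental assistant (oral health counsellor, OHC"). Procedures describes a first home visit and two further sessions. Controls have no counsellor; both arms keep the standard screening.

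Methods also reports the counsellors' ten-question knowledge test: the pre-training "mean score was 4.3 (SD = 1.49"), the post-training mean was 6.4 (SD 1.43), and the paired test gave p = 0.01. Competence is then followed by audio recording, integrity scoring and feedback. The number of counsellors is not given.

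Sample size and power states: "Sample size of approximately 514 children in each arm of the trial is required to detect a 35% reduction in dental decay experience", from "dmft 1.26 (SD 2.63), test dmft 0.8", "with a probability of 0.8 (power 80"%), "rejecting the likelihood of no difference at probability 0.05 (α = 0.05"). About 750 per arm are to be recruited, with a cited loss of 9% a year. No design effect or ICC appears.

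Data analysis lists t-tests, chi-square tests, and linear, logistic and Poisson regression. For the main comparison, "Univariate analyses will also be used to examine the association between the primary outcomes of dental decay incidence and prevalence", and obesity prevalence, with group allocation. Correlation is addressed once: site-level caries measures "will use GEE analysis to control for correlation within an individual".

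**The concern.** Motivational interviewing depends on the skill of the person delivering it, and the article expects that skill to need monitoring. If some counsellors achieve more than others, children with the same counsellor have correlated outcomes. That correlation exists in one arm only, so the design is partially nested. The named between-group methods, in their usual form, treat every child as independent.

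Two things are then at stake. Confidence intervals for the decay and obesity comparisons would be too narrow, and a chance set of better or worse counsellors could be read as an effect of the programme. The stated power would also be too high. This matters for the claim the article wants to make: its Discussion presents the trial as evidence that such personnel in general can be trained for the role, which goes beyond the individuals employed here.

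**Working it through.** **Inputs.** Sample size and power: 514 per arm, means 1.26 and 0.8 (difference 0.46), SD 2.63, α = 0.05 (taken as two-sided), 750 recruited per arm, 9% loss a year. Assumptions, because the article gives no figure: the ICC, and 10 counsellors (see step 2) with equal caseloads.

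**1. The plan's own figure.** n = 2 × (1.960 + 0.842)² × 2.63² / 0.46² = 513.1, rounded up to 514. Power at 514 is 80.1%. The figure is reproduced by the formula for independent observations, so it contains no allowance for counsellors.

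**2. How many counsellors.** Scores are whole numbers from 0 to 10, so not every group size can give the reported means and SDs. Checking n = 3 to 30:
- 3 to 9 cannot give them.
- 10, 11, 19 to 22 and 28 to 30 can.
- Adding the paired p-value (0.01 after rounding), 10 fits with a pre/post correlation between about −0.15 and 0.24, and 11 with about −0.32 to 0.11.
- 19 needs a correlation of about −0.92 or lower, which is implausible. From 20 upwards no correlation fits.

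This leaves 10 or 11 trainees, assuming complete pairs and the usual n − 1 SD. That the trainees are the counsellors who deliver is a further assumption. At 514 per arm it means about 51 or 47 children per counsellor.

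**3. Effect of counsellor clustering in one arm.**
- Design effect in the intervention arm: DE = 1 + (n/10 − 1) × ICC
- True SE = 2.63 × √((1 + DE)/n); unadjusted SE = 2.63 × √(2/n)
- Type I error of the unadjusted test = 2 × P(Z > 1.96 × unadjusted SE / true SE)
- Power = Φ(0.46 / true SE − 1.96)

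Example at n = 514, ICC 0.01: DE = 1 + 50.4 × 0.01 = 1.504; true SE = 0.1836 against 0.1641, a ratio of 1.12.

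Expected number analysed: 750 × 0.91³ ≈ 565, if the cited yearly rate, observed over two years, holds for three.

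| ICC | DE (514) | SE ratio (514) | Type I error (514) | Power at 514 | Power at 565 |
|---|---|---|---|---|---|
| 0 | 1.00 | 1.00 | 5.0% | 80.1% | 83.6% |
| 0.005 | 1.25 | 1.06 | 6.5% | 75% | 79% |
| 0.01 | 1.50 | 1.12 | 8.0% | 71% | 74% |
| 0.02 | 2.01 | 1.23 | 11.0% | 63% | 65% |

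With 11 counsellors at 514, the last three rows become 6.3%, 7.7% and 10.4% for type I error, and 76%, 72% and 64% for power. These are normal approximations; degrees of freedom suited to about 10 clusters would lower power further.

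**4. What the recruitment surplus absorbs.** At 565 per arm and 10 counsellors, power falls to 80% at an ICC of about 0.004. The surplus does not protect the type I error. With the number of counsellors fixed, caseloads grow, and at ICC 0.01 the error rises from 8.0% at 514 to 8.3% at 565.

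**5. Is the ICC range reasonable?** The between-counsellor SD is √ICC × 2.63: 0.19, 0.26 and 0.37 dmft for ICC 0.005, 0.01 and 0.02, or 40%, 57% and 81% of the expected effect of 0.46. ICC 0.05 gives 0.59, which exceeds the whole effect, so it is left out of the table.

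**The case against.** The strongest reply is that nothing in the article shows outcomes to vary by counsellor. Monitoring and feedback are meant to reduce such differences, and they may not carry through three short sessions to decay or body mass at 24 to 36 months. If counsellor effects vary by a third of the expected effect, the ICC is only about (0.46/3/2.63)² ≈ 0.003; type I error is then about 6%, and power at 565 is still about 80%. This stands, and it is why the point is conditional. If counselling affected no child at all, the unadjusted test would keep its 5% level; inflation needs counsellor effects that differ but average to zero.

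A second reply is that the article condenses a fuller plan, and a counsellor term may be specified in a statistical analysis plan not shown. That is possible. The article does, however, name its between-group tests and addresses correlation only within a child, and its sample size is fixed without a design effect.

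Third, a counsellor effect in the primary model is open to question. Counsellors who make home visits may cover areas, and the term would then absorb area differences that randomisation already balances. About 10 clusters also give an unstable variance estimate. Both stand, and they argue for a sensitivity analysis.

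**Conclusion.** The point holds conditionally. Intervention children share counsellors, control children do not, and neither the 514 per arm nor the named tests allow for it. For any positive counsellor ICC the planned standard errors are too small and 80% power at 514 is too high. With 10 counsellors and ICC 0.005 to 0.02, type I error is about 6.5% to 11%, and power about 75% to 63% at 514 or 79% to 65% at 565. The ICC is assumed, and the number of counsellors is inferred from training scores.

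A reader might infer more, and the documents do not support it:
- That the standard errors are in fact too small. No ICC is given, and at ICC 0 nothing changes.
- That there were fewer than 10 trainees. The whole-number scores rule out 3 to 9.
- That type I error reaches 19% with power of 46%. This needs ICC 0.05, a spread between counsellors larger than the effect the trial is designed to detect.
- That the primary models must be replaced. The case for that is debatable, for the reasons given under the objection.

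**What to change.** Record the counsellor for each intervention child, and state the number of counsellors. Prespecify a sensitivity analysis of the primary outcomes that allows for counsellor clustering in the intervention arm only, with controls as single observations: a random counsellor effect with Satterthwaite or Kenward-Roger degrees of freedom for continuous outcomes, and cluster-robust errors with a small-sample correction for counts and binary outcomes. Adjust it for the location stratum (Perth or Bunbury/Busselton), so that differences between those locations are not counted as counsellor effects. Report the estimated ICC, and state power over ICC 0 to 0.02 beside the 80%.

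The cost is one data field and one added analysis; no more children are needed. The downsides are somewhat wider intervals in that analysis, an imprecise variance estimate with about 10 counsellors, and a less favourable power statement. The data field matters most, because without it the analysis may not be possible later.
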